#### Secondary outcomes

3.Demographic characteristics of participants recruited to each arm: age, sex, ethnic group, highest educational attainment and area deprivation (measured by Index of Multiple Deprivation) will be recorded at baseline, which will enable us to determine if there are inequalities in retention and use of the online intervention (for those randomised to this arm).4.Outcome measures to be collected at baseline and at 3 months will include: Unit consumption of alcohol per week (using TOT-AL, an online beverage-specific measure [22] which requires participants to enter the type and quantity of alcohol drinks consumed on each day of the past week) Alcohol Use Disorders Identification Test (AUDIT) score [6], a method of screening for excessive drinking, developed by the World Health Organization (WHO) for use across a range of health settings Current psychological global distress score (using CORE-10 [23] developed and validated as a non-proprietary measure of psychological distress) Well-being scores (using EQ-5D [24]) Self-efficacy (using SCQ-8 [25]).5.Outcome measures to be collected at 3 months:Adherence to the intervention (for those randomised to this arm), measured through automated recording of numbers of log-ins and numbers of pages visited at each log-inOther sources of support accessed during treatment (e.g. group therapy; horticulture; acupuncture; art therapy; other therapies) Participant satisfaction with care (measured using the 8-item Client Satisfaction Questionnaire (CSQ-8), developed as a measure of satisfaction for mental health services, [26, 27] and used for assessing satisfaction with alcohol and other substance misuse programme) [28].

### Sample size

As this is a feasibility study a formal sample size calculation is not required, but we estimated the number of participants required as around 10 % of the number required for the Phase 3 trial [29]. The sample size calculation for the Phase 3 trial suggests we need to recruit 1665 participants. Given the participant population, a high level of attrition may be anticipated. We therefore aim to recruit 200 participants to the feasibility trial to inform the design and sample size of the Phase 3 RCT.

### Data handling and record keeping

Data from the website will be saved to a trial database which complies with the requirements of Good Clinical Practice and is maintained by the website developer. Data will be exported for analysis via UCL’s Identifiable Data Handling Solution (IDHS), which utilises a secure link to a secure drop box using ID numbers only and no identifying information. Participant contact details will be kept in a locked filing cabinet on university premises. Participant information at trial sites will also be kept securely according to local policies. The project has been registered with the UCL Data Protection Officer according to UCL Data Protection Policy.

### Statistical analysis

As this is a feasibility RCT, no hypothesis is to be tested. The aim of the trial is to determine estimates of recruitment and retention rates, to determine acceptability of the intervention and to provide parameters for the power calculation for a Phase 3 trial. Success criteria for recruitment and retention will be 84 and 75 %, respectively, as per the UKATT trial [30].

The analysis will be mainly descriptive. Descriptive statistics will be used to compare demographic characteristics of those completing each arm of the trial with those lost to follow-up. We will use multivariate logistic regression with robust confidence intervals (CI) to examine the impact of age, gender, ethnicity and deprivation level on these outcomes.

We will perform an analysis using regression of outcome on randomised group, adjusted for baseline value of outcome (for those outcomes measured at baseline) and other variables (age, gender, ethnicity and deprivation level) to compare the two arms using the following outcome measures at 3 months. Differences between the intervention and control groups for continuous variables with skewed distribution, e.g. alcohol consumption, will be log transformed, following a similar analysis to that by Wallace et al. [31]:Change in mean unit consumption of alcohol per week;Change in AUDIT score;Change in level of current psychological global distress score;Change in self-efficacy score;Acceptability of intervention using CSQ-8;Use of additional sources of support accessed during the trial period.

For the intervention group, we will examine adherence to the intervention, measured through automated recording of numbers of log-ins and numbers of pages visited at each log-in. We will conduct within-group analysis using linear regression to examine the impact of age, gender, ethnicity and deprivation on use of the intervention (number of log-ins, number of pages accessed, number of modules completed).

Missing data will be handled as follows:The primary analysis will be the mean difference in changes from baseline in all outcome variables between intervention and control groups at 3 months, using all available results but without imputation of missing data. Secondary analyses will include all randomised individuals by assuming that non-responders have no change in any missing outcome measures;For use of the intervention, data will be largely complete as automatically collected by the website.

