### Data collection

If the client wishes to participate, they will be allocated a trial identification number linked to their email address and mobile phone number. All data will be collected anonymously online. All participants will be emailed a link to complete the baseline data collection questionnaires (see outcome measures, below). After they have completed the questionnaires, they will then be individually randomised by computer to the intervention or TAU. Those randomised to the intervention will be emailed a link to HeLP-Alcohol and those randomised to TAU will be directed back to their community alcohol service. All participants will be emailed another request for follow-up data collection 3 months after randomisation. For those participants who do not respond to the first email, there will be another two follow-up emails and then a phone call or text message request. See Fig. 1 for CONSORT participant flow diagram [21].

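### The planned attrition analysis looks at demographics only, so the trial will not describe whether loss to follow-up is related to drinking severity, or differently so by arm, although baseline severity is known for everyone randomised.

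*Protocol article*

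**What the plan says.** All references are to the protocol article.

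- **Who is lost (Statistical analysis).** "Descriptive statistics will be used to compare demographic characteristics of those completing each arm of the trial with those lost to follow-up". The next sentence plans a logistic regression to "examine the impact of age, gender, ethnicity and deprivation level on these outcomes". I read its outcome as completion versus loss. No baseline drinking measure and no arm term is named.
- **Between-arm regression (Statistical analysis).** Each 3-month outcome is regressed on randomised group, "adjusted for baseline value of outcome (for those outcomes measured at baseline"), plus age, gender, ethnicity and deprivation.
- **Missing data (Statistical analysis).** The primary analysis is described as a mean difference between arms in change from baseline, "using all available results but without imputation of missing data". Then: "Secondary analyses will include all randomised individuals by assuming that non-responders have no change in any missing outcome measures".
- **What is known at baseline.** Secondary outcomes gives the list headed "Outcome measures to be collected at baseline and at 3 months will include": weekly units, AUDIT, CORE-10, EQ-5D and SCQ-8. Under Data collection the order is fixed: "After they have completed the questionnaires, they will then be individually randomised by computer to the intervention or TAU". These measures should therefore be on file for every randomised person, including those later lost.
- **Context.** Primary outcomes lists retention by arm. Sample size anticipates high attrition. Statistical analysis sets the retention criterion at 75%.

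**The concern.** The trial is meant to tell the Phase 3 team how many people will be kept and what that loss implies. A demographic comparison answers a question about inequalities, which is the reason given under Secondary outcomes for collecting demographics. It does not show whether the people lost were the heavier drinkers, or whether that differed between the web and face-to-face arms. Those lost could match completers on age, sex, ethnicity and deprivation while one arm had lost its heaviest drinkers, and nothing in the planned output would reveal it.

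At stake are the interpretation of the retention result and, depending on which analysis is run, the arm comparison at 3 months. This is more than detail left for an analysis plan: the article states its attrition method and limits it to named demographic variables.

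**Working it through.** The plan states no figure for this point, so there is none to reproduce. The size is worked from its own Phase 3 inputs.

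**Inputs**
- SD of consumption at follow-up: 85% of the mean (Discussion). I assume the same SD at baseline.
- Correlation r between baseline and follow-up consumption: 0.40 (Discussion).
- Loss: 25%, the complement of the 75% retention criterion, assumed in both arms.
- Target sample: 200 (Sample size), giving 150 completers and 50 lost, or about 75 and 25 per arm.
- g: the amount, in SD, by which the lost exceeded completers at baseline in one arm, with no gap in the other. The document gives no value, so g is an assumption.

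**1. Unadjusted difference in change.** In the affected arm, completers start 0.25 × g SD below everyone randomised. Expected change falls by (1 − r) SD for each SD of baseline, so

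bias = 0.25 × g × (1 − 0.40) × 85% of the mean = 12.75% × g.

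| Assumed g | Bias, % of mean | Share of the 15% Phase 3 difference |
|---|---|---|
| 0.12 | 1.5 | 10% |
| 0.25 | 3.2 | 21% |
| 0.50 | 6.4 | 43% |

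These figures are on the untransformed scale. The plan log-transforms skewed outcomes, so they indicate size only.

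**2. Regression adjusted for baseline.** In a simulation of 2,000,000 people with no true effect, 25% lost in each arm, and loss tied to baseline drinking in one arm only (assumed log-odds 0.8 per SD), the adjusted available-case estimate had bias 0.00 SD. The unadjusted change difference had bias +0.11 SD, about 9% of the mean; the baseline gap in that setting was 0.72 SD.

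**3. No-change secondary analysis.** In the same simulation its bias was +0.08 SD, about 7% of the mean. This follows from step 1: setting the lost 25% to zero change multiplies the completers' difference by 0.75, and 0.75 × 0.11 = 0.08. It errs in the same direction as the unadjusted analysis, so agreement between the two would not be reassuring.

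**4. Outcomes without a baseline value.** CSQ-8 and use of additional support are collected only at 3 months, so their models hold demographics alone. If such an outcome has correlation ρ with baseline severity given the demographics, the bias is 0.25 × g × ρ SD. The document gives no ρ. At g = 0.50 the bias cannot exceed 0.25 × 0.50 = 0.125 SD, even with ρ = 1.

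**5. Loss that depends on 3-month drinking.** With the same assumed strength, the adjusted estimate was biased by −0.15 SD (about −13% of the mean) and the no-change analysis by −0.08 SD (about −7%). The baseline gap in the affected arm was then only 0.29 SD.

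**6. What the extended comparison can show.**
- Whole trial: 95% half-width = 1.96 × √(1/150 + 1/50) = 0.32 SD; detectable with 80% power = 2.80 × √(1/150 + 1/50) = 0.46 SD.
- Within one arm: half-width = 1.96 × √(1/75 + 1/25) = 0.45 SD; detectable = 0.65 SD.
- Difference in gap between arms: detectable = √2 × 0.65 ≈ 0.91 SD.

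**The case against.** **The regression already adjusts for baseline.** This is the strongest reply, and it stands for weekly units. A reader might infer from step 1 that the planned drinking comparison is biased by 3 to 6% of the mean. The document does not support that if the baseline-adjusted regression is the primary analysis, and the regression and missing-data paragraphs can be read together in that way. The missing-data paragraph, however, defines the primary analysis as a difference in change without repeating the adjustment. The adjustment also cannot reach outcomes that have no baseline value.

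**Nobody is dropped from the secondary analysis.** Correct. It would be wrong to say that the plan simply discards people without 3-month data: that is true of the primary analysis only. But the no-change rule is one fixed assumption and does not describe who is lost.

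**The protocol does not forecast arm-specific dropout.** Also correct. The Discussion's remark about clients who might disengage if not seen face-to-face concerns whom counsellors invite, and the authors label it selection bias. It should not be cited as a prediction of differential loss after randomisation.

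**The added comparison is weak.** With about 50 losses, none of the gaps in the table would be reliably detected within an arm. A reader might infer that the extension would detect outcome-related dropout. It would not: with r = 0.40, baseline drinking is a poor proxy for unseen 3-month drinking. This is a reason to report estimates with intervals and to avoid tests, but not to leave out the comparison.

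**The stakes are modest.** The trial tests no hypothesis, the 15% Phase 3 difference is set by design, and the observed follow-up rate is correct whoever drops out. With 75 completers per arm the adjusted difference has SE 0.85 × √0.84 × √(2/75) = 12.7% of the mean, a 95% interval of about ±25%. The biases above are small beside that. This limits the harm to the arm comparison, but not the gap in describing retention.

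**Conclusion.** The point holds in a limited form. The stated attrition analysis covers demographics only, so loss related to drinking severity, or differing by arm in that respect, will not be described, although the needed data should be held for everyone randomised.

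For weekly units, loss driven by baseline drinking leaves the baseline-adjusted regression unbiased, provided that the model is right. It would bias an unadjusted difference in change by about 3% of the mean at an assumed gap of 0.25 SD in one arm with 25% lost. The models for satisfaction and additional support have no protection against it, but the size there cannot be calculated from the document. These results assume equal SDs at baseline and follow-up, equal loss in both arms and a linear relation between baseline and follow-up.

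The improvement is worth making because retention is a primary outcome and the cost is close to nil. It is not evidence that the planned drinking estimate is wrong.

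**What to change.** In the Statistical analysis section:

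1. Extend the comparison of completers with those lost, by arm, to baseline weekly units, AUDIT, CORE-10 and SCQ-8.
2. Add arm, baseline units (log scale) and AUDIT to the retention logistic model. Report estimates with confidence intervals, not tests.
3. State that the primary available-case comparison is the regression adjusted for the baseline value of the outcome.
4. For outcomes measured only at 3 months, name baseline AUDIT or baseline units in advance as a covariate. Do not choose covariates according to whether they appear to predict loss: with about 50 losses that selection would be unstable and data-driven.

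**Cost.** Wording and a few more table rows and model terms; no new data and no change to the sample size. The intervals will be wide (about ±0.32 SD overall, ±0.45 SD within an arm). The report should say that an unremarkable baseline comparison does not rule out loss related to unobserved 3-month drinking.

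### Education is collected to study inequalities in retention and use but is in neither regression model, and plain linear regression of the usage counts gives miscalibrated intervals when use differs by subgroup

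*Protocol article*

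**What the plan says.** **Purpose.** Under Secondary outcomes, the article lists age, sex and ethnic group, and adds that "highest educational attainment and area deprivation (measured by Index of Multiple Deprivation) will be recorded at baseline". The reason follows directly: "which will enable us to determine if there are inequalities in retention and use of the online intervention".

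**Retention.** Statistical analysis first plans a descriptive comparison of the demographic characteristics of "those completing each arm of the trial with those lost to follow-up". It continues: "We will use multivariate logistic regression with robust confidence intervals (CI) to examine the impact of age, gender, ethnicity and deprivation level on these outcomes".

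**Use.** For the web arm the same section says: "We will conduct within-group analysis using linear regression to examine the impact of age, gender, ethnicity and deprivation on use of the intervention". Use means three counts: log-ins, pages and modules.

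**Scope of the safeguards.** Robust intervals are mentioned for the logistic model only. The log-transformation rule concerns differences between the arms in skewed continuous variables, so it does not reach this within-arm analysis.

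**The concern.** The article gives five demographics a common purpose and then carries four of them into the models that serve it. The one left out is the only individual-level socioeconomic measure; the deprivation variable that remains is an area index. The Background names a widening digital divide among the challenges that justify a feasibility trial, and the Discussion makes equality of access a question for the definitive trial. If education is not modelled, the trial may end with an area-level answer to a question partly about individuals, although the data are in hand.

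The usage model is a second, smaller matter. The Background expects low engagement and fall-off, which makes skewed counts with many low values plausible. Ordinary linear regression assumes one common variance, whereas for such counts the variance rises with the mean. If a subgroup uses the site less, or more, the common-variance interval has the wrong width. That is the situation the analysis is meant to describe.

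**Working it through.** **1. Purpose against models.**

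| Recorded to study inequality | Retention model | Usage model |
|---|---|---|
| Age | yes | yes |
| Sex/gender | yes | yes |
| Ethnic group | yes | yes |
| Highest educational attainment | **no** | **no** |
| Area deprivation | yes | yes |

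Education still enters the descriptive comparison of completers with those lost, because Secondary outcomes counts it among the demographic characteristics. No analysis of use mentions it.

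**2. Room for education.** Inputs from the article: 200 participants, a 50% chance of the website, and 75% retention as the success criterion.

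- Expected losses: 200 × 0.25 = 50. Web arm: 200 × 0.5 = 100.
- Take one parameter for each of the four listed covariates (an assumption, with ethnicity collapsed to two groups): 50/4 = 12.5 losses per parameter.
- Education in two levels: 50/5 = 10. In three levels: 50/6 = 8.3.

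This is tight but workable for an exploratory model.

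**3. Linear regression of the counts.** The article gives no usage distribution and no figure to reproduce, so all values here are assumed: 70 participants with mean 4 log-ins, a subgroup of 30 with mean 2 (halved) or 8 (doubled), and variance m + αm² with dispersion α = 1.

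- Variances: mean 4 gives 4 + 16 = 20; mean 2 gives 2 + 4 = 6; mean 8 gives 8 + 64 = 72.
- True variance of the mean difference, halved: 20/70 + 6/30 = 0.486. Doubled: 20/70 + 72/30 = 2.686.
- Variance that linear regression reports (pooled variance × (1/70 + 1/30), where the bracket is 0.0476):
  - halved: (70×20 + 30×6)/100 = 15.8, giving 0.752;
  - doubled: (70×20 + 30×72)/100 = 35.6, giving 1.695.
- Reported over true standard error, halved: √(0.752/0.486) = 1.24. Doubled: √(1.695/2.686) = 0.79.
- Large-sample coverage of a nominal 95% interval, halved: 2Φ(1.96 × 1.24) − 1 ≈ 0.985. Doubled: 2Φ(1.96 × 0.79) − 1 ≈ 0.88.

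Simulation under the same assumptions, which also reflects skewness, gives about 0.97 and 0.86. With mean 3, a 25% subgroup and dispersion 1 or 2, coverage is 0.98–0.99 for halved use, 0.85 for doubled use, and 0.947–0.948 with no difference.

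**4. Which remedy.** Share of simulated trials in which the 95% interval excludes no difference, for halved use (n = 100, 30% subgroup, mean 4):

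| Method | Dispersion 1 | Dispersion 2 |
|---|---|---|
| Linear, common variance | 67% | 38% |
| Linear, HC3 robust errors | 81% | 60% |
| Negative binomial | 78% | 56% |

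The rows come from separate runs, so gaps of a few points mean little. Robust errors recover what the common-variance interval loses. They are not perfect: for doubled use in the mean-3 setting, HC3 coverage is 0.91 to 0.93, still better than 0.85.

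**The case against.** The best defence is that the plan is mainly descriptive and tests no hypothesis, so power is not the yardstick. With about 100 people in the web arm, a short covariate list is a reasonable choice. This stands as a reason to treat the point as minor. It does not explain why a variable collected for a stated purpose is missing from both models that serve it, and interval coverage matters for estimation with or without a test.

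Four stronger readings are tempting, and the document does not support them:

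- **That the education gradient is examined nowhere.** For retention it is, through the descriptive comparison of demographic characteristics. Only the usage analysis lacks it altogether.
- **That leaving randomised arm out of the retention model is an error.** The outcome models do name it ("regression of outcome on randomised group, adjusted for baseline value of outcome") and the retention model does not. But the retention sentence follows a comparison worded by arm, so separate models per arm are a fair reading, and retention is already a primary outcome reported for each arm. In a large simulated sample with an arm log-odds effect of −1.0, omitting arm moved a covariate effect only from −0.70 to −0.66. An effect confined to the web arm would be roughly halved by pooling (−1.0 appears as −0.53), but an interaction would rest on about 25 losses per arm. That is a trade-off, not a mistake.
- **That linear regression gives wrong estimates.** It estimates mean differences without bias; only its intervals are at fault.
- **That a negative binomial model is required.** Robust intervals do about as well for halved use. Modules completed is probably a bounded count in a three-phase, 6-week programme, for which a negative binomial is a doubtful default.

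**Conclusion.** The point holds, at minor severity. The omission of education from both regression models contradicts the article's own reason for collecting it. This follows from the text alone and rests on no assumption. The gap is complete for use and partial for retention.

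The usage intervals are a secondary weakness. Under assumed skewed counts, nominal 95% coverage is about 0.97 when a subgroup uses the site half as much and about 0.86 when it uses it twice as much; it is close to nominal when use does not differ. These sizes depend on the assumed mean, dispersion and subgroup share, none of which the article gives.

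Nothing here affects the primary outcomes, the 84% and 75% success criteria, or the parameters for the Phase 3 calculation.

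**What to change.** 1. Add highest educational attainment, collapsed to two or three levels, to the logistic model for retention and to the usage models.
2. For log-ins and pages, either use a count model such as negative binomial, reporting rate ratios with 95% intervals, or keep linear regression and extend the robust intervals already planned for the logistic model.
3. For modules completed, extend the robust intervals.
4. Optionally, say in one clause whether the retention model is fitted by arm. No interaction term is needed.

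The cost is wording only, since every variable is already collected. The statistical price is one or two more parameters, taking the retention model from 12.5 to between 10 and 8.3 expected losses per parameter on the count above.

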**Conclusion:**

The proposed trial will provide data to inform a fully powered non-inferiority effectiveness and cost-effectiveness RCT comparing HeLP-Alcohol with TAU.

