The proposed feasibility study is therefore important in order to identify these challenges prior to designing the Phase 3 trial, to test online data collection, randomisation methods and the prompts to encourage continued use of the intervention. Data from this study will also be used to refine the sample size calculation for the Phase 3 RCT. Our hypothesis is that supported access to HeLP-Alcohol is of equal effectiveness as TAU. The RCT will be designed to have 90 % power to detect (at a 5 % significance level) a difference in mean weekly alcohol consumption of 15 % between intervention and TAU groups (if such a difference occurs). The assumptions are (i) standard deviation of alcohol consumption at follow-up is equal to 85 % of the mean and (ii) a correlation between baseline and follow-up alcohol consumption of 0.40, as found in a previous RCT of an online alcohol intervention [30]; (iii) a follow-up rate of 75 % at 12 months, based on the experience of UKATT [33]; (iv) an intra-cluster correlation of 0.02 for the effect of alcohol counsellors, also based on the UKATT trial. The standard error of the mean difference in alcohol consumption will be about 5 %, so an estimated zero difference would have a 95 % confidence interval of −10 to +10 %. The definitive trial therefore requires 1665 participants.

If the definitive study shows that a web-based alcohol treatment programme is as effective as face to face treatment, then implementation of such a programme could increase patient choice, improve access to alcohol treatment for hazardous and harmful drinkers and lead to cost savings for treatment services and more widely for the NHS in treating alcohol-related health conditions, particularly for people who are reluctant or unable to attend face-to-face services.

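### The only all-randomised outcome analysis assumes no change in non-responders, which shrinks real arm differences, can create false ones, and is undefined for outcomes without a baseline

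*Protocol article*

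**What the plan says.** The Statistical analysis section of the protocol article sets two missing-data rules for the 3-month outcomes. The primary comparison of changes is made "using all available results but without imputation of missing data". Then: "Secondary analyses will include all randomised individuals by assuming that non-responders have no change in any missing outcome measures". No other analysis of outcomes in all randomised people is described.

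The same section states that "As this is a feasibility RCT, no hypothesis is to be tested" and that one purpose of the trial is "to provide parameters for the power calculation for a Phase 3 trial". The Discussion adds: "Data from this study will also be used to refine the sample size calculation for the Phase 3 RCT". Neither place names the dataset from which those parameters will be taken. The Conclusion of the abstract describes Phase 3 as a "fully powered non-inferiority effectiveness and cost-effectiveness RCT comparing HeLP-Alcohol with TAU".

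On expected non-response, the Statistical analysis section states: "Success criteria for recruitment and retention will be 84 and 75 %, respectively". The Sample size section adds: "Given the participant population, a high level of attrition may be anticipated". No arm-specific rates are given.

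**The concern.** Setting a missing 3-month value equal to the baseline value claims to know, with certainty, that the person did not change. Three problems follow.

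- **Bias.** Participants come to alcohol services for help, so drinking is likely to fall in both arms. Each non-responder is then entered with a change of zero. Equal non-response shrinks any real difference. Unequal non-response, which a web versus face-to-face comparison invites, produces a difference where there is none.
- **False precision.** Imputed values are analysed as if they had been observed.
- **No definition.** The rule covers any missing outcome. CSQ-8 and use of additional support are on the list of arm comparisons but, under Outcome measures, are collected only at 3 months. There is no baseline to carry forward.

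An all-randomised analysis is there to test the available-case result. This one leans towards similarity when non-response is balanced, which is the unhelpful direction for a programme heading to non-inferiority. When non-response is unbalanced it can mislead against the arm with more of it. A further, conditional risk is that its baseline/follow-up correlation is carried into the Phase 3 calculation.

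**Working it through.** **Inputs from the protocol article.** Retention criterion 75%, so non-response q = 25%. From the Discussion: SD at follow-up 85% of the mean, correlation r = 0.40, target difference 15%, 90% power, 5% significance (taken as two-sided), 75% follow-up, intra-cluster correlation 0.02, N = 1665. From Sample size: 200 participants in the present trial.

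**Assumptions, not in the documents.** Baseline mean 40 and 3-month mean 28 units (a 30% fall); non-response unrelated to outcome; where stated, 35% v 15% non-response; counsellor cluster size m = 6.

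**1. Arm difference under the rule.** With mean change d in each arm, the imputed difference is (1 − q_web) × d_web − (1 − q_TAU) × d_TAU.

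- *Equal non-response, 25% in both arms.* A true 15% difference becomes 0.75 × 15 = 11.25%. In units, 4.2 (15% of 28) becomes 3.15. A true zero stays zero.
- *35% web, 15% TAU, true zero.* 0.65 × (−30%) − 0.85 × (−30%) = +6 points of baseline. That is 2.4 units of 40, or 2.4/28 = 8.6% of the 3-month mean.
- *40% web, 25% TAU, true zero.* 0.60 × (−30%) − 0.75 × (−30%) = +4.5 points of baseline, in favour of TAU.

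**2. Simulation.** Correlated lognormal outcomes were analysed by regression adjusted for baseline.

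| Scenario | True difference | No-change estimate | Coverage of 95% CI, n = 200 | Coverage, n = 2000 |
|---|---|---|---|---|
| 25% / 25% | 4.2 | about 3.1 | about 93% | about 81–85% |
| 35% / 15% | 0 | about 2.3–2.4 (about 8% of 28) | about 87% | about 32% |

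The available-case regression was unbiased in both. At n = 200 the bias of about 1.1 or 2.3 units compares with a sampling SD of about 3.1. Standard errors under the rule were about 8–13% smaller than available-case, and 15% smaller in one set-up (3.12 v 3.68), although no information had been added. On the log scale, which the protocol plans for skewed outcomes, the 35%/15% bias is about 7% with coverage 88% at n = 200.

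**3. The plan's Phase 3 figure.** Two-sample formula: 675 per arm. Times (1 − 0.40²) = 0.84 gives 567 per arm, 1134 in total. Divided by 0.75 gives 1512. Times a design effect of 1 + 5 × 0.02 = 1.10 gives 1663, against the stated 1665. The cluster size is not stated; m = 5 to 7 gives 1633 to 1693.

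**4. Correlation in the imputed set.** With equal SDs and no mean change it is (1 − q) × r + q = 0.75 × 0.40 + 0.25 = 0.55. The lognormal model gives 0.57. The effect on N depends on how the SD is also taken:

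- r = 0.55, SD held at 85% of the mean: factor (1 − 0.55²)/0.84 = 0.698/0.84, N about 1381.
- Lognormal model, r = 0.57, SD also from the imputed set as a percentage of the mean (85% rises to 88%): N about 15% lower.
- The same, with SD in units (23.8 rises to 27.2) and a fixed 4.2-unit difference: N about 4% higher.

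**The case against.** The strongest reply is about weight. The rule is secondary, the main comparison uses unimputed data, the trial tests no hypothesis, and its primary outcomes are recruitment and retention, which imputation does not touch. Any gap between the two analyses will be visible to the reader. This stands, and it limits the harm. It does not rescue the rule: a sensitivity analysis is worth having only if it tests the main result under plausible departures, and this is the only one offered.

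A reader might infer that the rule corrupts the correlation handed to Phase 3. The documents do not support that. They name no source dataset, and the present 0.40 comes from an earlier online trial. Nor do they support a fixed shortfall of about 20% in Phase 3: that figure changes r (0.40 to 0.57) and ignores the rise in SD that the same imputation causes. The poor coverages at n = 2000 do not describe a trial of 200.

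The spurious difference needs unequal non-response, and the documents give no rates by arm. That also stands; the 8% is illustrative.

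Multiple imputation from the covariates already in the regression would largely repeat the available-case result. This is fair for that step alone. Log-ins add information in the web arm, and the delta analysis supplies the real test.

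The gap for CSQ-8 and additional support can be closed with one clause, since the section elsewhere distinguishes outcomes measured at baseline. That is true, but the rule as worded does not make the exception.

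**Conclusion.** The concern holds in limited form. The shrinkage by a quarter (15% to about 11%) follows from the protocol's own 75% retention criterion, provided non-response is equal and non-responders change as responders do. The spurious difference of about 8% against the arm with more non-response rests on an assumed 35% v 15% split and a 30% fall. The understated standard errors (about 8–13%) come from simulation under an assumed lognormal model. That the rule is undefined for CSQ-8 and additional support needs no assumption.

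At n = 200 the loss of coverage is modest (about 93% and 87%), and the primary analysis is not affected. The effect on Phase 3 is conditional: a correlation taken from the imputed set would be about 0.55–0.57 instead of 0.40, but the documents do not say it will be, and the net change in N could go either way. The change is worth making because a stated biased rule can be replaced cheaply by a better one.

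**What to change.** - Replace the no-change rule as the all-randomised sensitivity analysis, or keep it only as one labelled scenario. Use multiple imputation by arm, with baseline outcomes, the covariates already listed (age, gender, ethnicity, deprivation) and, in the web arm, log-ins.
- Add an arm-specific delta analysis in which web-arm non-responders are set progressively worse than imputed, up to the 15% difference used for Phase 3.
- State that outcomes with no baseline (CSQ-8, additional support) are excluded from any no-change rule.
- State that the SD and correlation for Phase 3 will be estimated from observed baseline/3-month pairs only.

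The cost is modest extra programming and a few sentences in the analysis section. No new data are needed, since log-ins are already recorded automatically.
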